## Abstract

**Background:**

There is a need to better distinguish viral infections from antibiotic-requiring bacterial infections in children presenting with clinical community-acquired pneumonia (CAP) to assist health care workers in decision making and to improve the rational use of antibiotics.

**Objective:**

The overall aim of the Trial of Respiratory infections in children for ENhanced Diagnostics (TREND) study is to improve the differential diagnosis of bacterial and viral etiologies in children aged below 5 years with clinical CAP, by evaluating myxovirus resistance protein A (MxA) as a biomarker for viral CAP and by evaluating an existing (multianalyte point-of-care antigen detection test system [mariPOC respi] ArcDia International Oy Ltd.) and a potential future point-of-care test for respiratory pathogens.

**Methods:**

Children aged 1 to 59 months with clinical CAP as well as healthy, hospital-based, asymptomatic controls will be included at a pediatric emergency hospital in Stockholm, Sweden. Blood (analyzed for MxA and C-reactive protein) and nasopharyngeal samples (analyzed with real-time polymerase chain reaction as the gold standard and antigen-based mariPOC respi test as well as saved for future analyses of a novel recombinase polymerase amplification–based point-of-care test for respiratory pathogens) will be collected. A newly developed algorithm for the classification of CAP etiology will be used as the reference standard.

**Results:**

A pilot study was performed from June to August 2017. The enrollment of study subjects started in November 2017. Results are expected by the end of 2019.

**Conclusions:**

The findings from the TREND study can be an important step to improve the management of children with clinical CAP.

**International Registered Report Identifier (IRRID):**

DERR1-10.2196/12705

## Introduction

### Biomarkers in Pediatric Respiratory Tract Infections

Respiratory infection is a common reason among children for seeking care [1]. The majority of respiratory infections in children are caused by viruses [2]. Nevertheless, viral and bacterial infections are hard to distinguish clinically, causing many children with viral infections or self-limiting bacterial infections to receive unnecessary antibiotic treatment, which contributes to the development and spread of antibiotic resistance [3,4]. There is a need for new biomarkers that better distinguish viral infections from antibiotic-requiring bacterial infections in children presenting with clinical community-acquired pneumonia (CAP) and that assist health care workers in decision making and improving the rational use of antibiotics [5].

C-reactive protein (CRP), procalcitonin (PCT), and white blood cell (WBC) count are the most commonly used inflammatory markers in clinical practice for the management of children with suspected CAP [6,7]. There is increasing evidence that PCT is superior to CRP as a screening test for serious bacterial infection given the favorable kinetics, including a more rapid response to inflammation [8]. However, neither of the biomarkers have been proven to be reliable in differentiating between mild or moderate bacterial and viral CAP [9,10]. A WBC count of 15,000/μl has been suggested as a cutoff to differentiate between viral and bacterial etiologies. However, critically ill patients with neutropenia will not have an increased WBC count, and certain viruses such as influenza and adenovirus can elicit a strong immune response with a high WBC count greater than 15,000/μl [11]. Neither is a complete blood count reliable in differentiating between bacterial and viral CAP in children [6]. To date, most biomarkers used in clinical practice have been selected for their ability to identify serious bacterial infections, and there is a need for novel biomarkers that can reliably detect *viral* infections [12].

Myxovirus resistance protein A (MxA) is an intracellular protein that is upregulated upon activation of the antiviral defense system. Increased blood MxA has been reported to be specific for viral infection [13-15]. There is a commercially available rapid diagnostic test, FebriDx, that qualitatively detects MxA and CRP at cutoffs of 40 ng/ml and 20 mg/ml, respectively. The test has been reported to have 85% (29/34) sensitivity and 93.4% (183/196) specificity to rule out a bacterial infection in patients (adults and children) with febrile respiratory infection [16]. However, no studies have focused on MxA in children with CAP. It was previously shown that virus-positive asymptomatic children had lower MxA levels as compared with virus-positive symptomatic children with respiratory symptoms [14]. As current viral real-time polymerase chain reaction (PCR) testing of upper respiratory specimens (ie, the routine method for diagnosing respiratory tract infections) is complicated by frequent asymptomatic detection, MxA has the potential to facilitate the interpretation of viral PCR positivity in terms of clinical relevance in children with CAP [17].

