### Classification of Etiology in the Trial of Respiratory Infections in Children for Enhanced Diagnostics Study

The algorithm for classifying etiology in the TREND study is based on the current literature and will classify children into viral, bacterial, atypical bacterial, mixed viral-bacterial, and undetermined infections based on clinical, microbiological, radiographic, and biochemical findings (Figure 2). A second, stricter algorithm only considering microbiologically confirmed diagnoses will be used in a complementary subanalysis (Figure 3).

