### A New Algorithm for Classification of Etiology in Pediatric Community-Acquired Pneumonia Studies

One major weakness in the studies of diagnostic biomarkers in pediatric infectious diseases is the lack of a reliable gold standard for the microbiological diagnosis [5,49]. The gold standard for assigning bacterial etiology has traditionally been the detection of bacteria in cultures from normally sterile sites (lung, blood, and pleura). However, as sampling from the lung/pleura is infeasible in most cases and blood cultures have limited sensitivity, this approach is of little use in clinical studies of CAP [5]. Previous studies assessing the performance of diagnostic tests in terms of distinguishing bacterial infections from viral infections have used either an independent expert panel or a laboratory-/radiological-based approach to classify disease etiology [12-15]. Both approaches have their advantages and limitations. Using a strict microbiologically confirmed diagnosis as the reference has the advantage of high specificity, but the generalizability of the findings is hampered as the majority of children in clinical practice will not have a clear microbiologically confirmed diagnosis. In addition, for a diagnostic test to be useful, it is more important to distinguish between etiologically less clear cases of respiratory infections rather than to identify the school book examples of bacterial and viral infections. In the TREND study, we chose a more pragmatic approach favoring generalizability for microbiological accuracy. However, given that doctors in expert panels rely on microbiological and biochemical findings, we reasoned that it still would be more stringent to create an algorithm for the classification of etiology. In the TREND study, a diagnostic algorithm has been created a priori to serve as the reference based on the current evidence for the classification of CAP etiology. Detection of RSV, hMPV, influenza virus, and PIV has, in previous case-control studies, been highly associated with CAP. Furthermore, these viruses appear to be rarely detected in asymptomatic individuals, and hence, detection will be considered to be a definitive indicator of etiology [21,22,47,50,51]. For other respiratory viruses as well as for the atypical bacteria *M pneumoniae*, the clinical significance of PCR positivity is less clear owing to frequent detections in asymptomatic children [17,52-55]. For that reason, PCR positivity will not be considered enough for establishing etiology. Virkki et al reported that a CRP level of more than 80 in children aged less than or equal to 2 years and more than 120 in children aged 2 to 5 years was specific (>85%) for bacterial etiology, whereas a CRP level of less than 20 was specific for viral etiology (78%) [56]. These cutoffs will be used to aid in the definition of probable bacterial and viral infections in less clear cases. Hence, detection of viruses other than influenza, RSV, hMPV, and PIV will be considered as viral infections only if the CRP value is less than 20. Given that adenovirus has been associated with high CRP, this rule will not be applicable for adenovirus [11]. However, adenovirus detections will not be considered in the strict algorithm, as asymptomatic detection of the virus is common [17]. Finally, given that CRP levels depend on the disease duration and to avoid false-negative test results (ie, low but rising CRP values), an additional criterion of reported fever duration of more than 24 hours will be applied in the TREND study when considering CRP levels [45]. As discussed above, there is no optimal reference standard for the classification of CAP etiology, neither clinically nor in research. However, we believe that much is to be gained if we use an algorithm instead of an expert panel. The decisions taken by expert panels differ between different studies, over time, and between different settings. When using an algorithm, this can be controlled for. We look forward to comments and inputs on our algorithm so that together we can develop it further.

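### Where a CRP cutoff decides the viral or bacterial label, a CRP error is scored against MxA or the child may drop out, so MxA results should be reported by how the label was reached.

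*Protocol article*

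**What the plan says.** All references are to the protocol article.

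- **Abstract, Methods:** "A newly developed algorithm for the classification of CAP etiology will be used as the reference standard". The first specific objective, at the end of the Introduction, is the diagnostic accuracy of MxA for viral CAP.
- **Introduction, Biomarkers in Pediatric Respiratory Tract Infections:** of CRP and procalcitonin, "neither of the biomarkers have been proven to be reliable in differentiating between mild or moderate bacterial and viral CAP".
- **Methods, Classification of Etiology:** children are sorted into "viral, bacterial, atypical bacterial, mixed viral-bacterial, and undetermined infections based on clinical, microbiological, radiographic, and biochemical findings". A stricter, microbiologically confirmed version is a complementary subanalysis.
- **Discussion, A New Algorithm for Classification of Etiology:** for RSV, hMPV, influenza and PIV, "detection will be considered to be a definitive indicator of etiology". Otherwise, "detection of viruses other than influenza, RSV, hMPV, and PIV will be considered as viral infections only if the CRP value is less than 20", with adenovirus exempt from this rule. On the CRP cutoffs (below 20; above 80 up to age 2 years; above 120 from 2 to 5 years): "These cutoffs will be used to aid in the definition of probable bacterial and viral infections in less clear cases". The cited specificities are 78% for CRP below 20 (viral) and above 85% for the high cutoffs (bacterial). CRP is considered only with more than 24 hours of reported fever.
- **Same section, on what makes a test useful:** "it is more important to distinguish between etiologically less clear cases of respiratory infections", rather than to recognise textbook examples.

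**The concern.** MxA is studied because existing markers, CRP among them, are not proven to separate viral from bacterial CAP in milder disease. Yet part of the reference against which MxA is judged is set with CRP. In that part, a child whom CRP places in the wrong class and MxA reads correctly is recorded as an MxA failure. If MxA errs along with CRP, the agreement is recorded as a success.

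There is also a selection effect. A child with one of the less specific viruses and a CRP of 20 or more fails the viral rule. If CRP is also below the high cutoff, the child may end up undetermined and leave the viral versus bacterial comparison.

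Both effects fall on the less clear cases, which the article itself says matter most for a useful test. If the two routes to a label are pooled, a reader cannot tell how far an MxA result reflects etiology and how far it reflects agreement with CRP.

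**Working it through.** **1. The plan's own figures reproduce.** From Study Size and Power Calculation: difference 500 µg/l, SDs 1000 and 300, two-sided alpha 0.05, power 80%, plus 20%.

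- n per group = (1000² + 300²) × (1.960 + 0.842)² / 500² = 34.2, rounded up to 35; 35 × 1.2 = 42.
- Cases: 42 / 0.14 = 300. Expected viral cases: 300 × 0.45 = 135. Expected bacterial cases: 300 × 0.14 = 42.

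The point below contests none of these.

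**2. Which labels can depend on CRP, from the text alone.**

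| Finding | Role of CRP |
|---|---|
| RSV, hMPV, influenza or PIV by PCR | CRP below 20 not needed for a viral finding |
| Adenovirus | exempt from the CRP rule in the main algorithm; ignored in the strict one |
| Other virus, CRP below 20 | viral label depends on CRP (and on the detected virus) |
| Other virus, CRP of 20 or more | viral label refused; may be undetermined, mixed or bacterial |
| CRP above 80 or 120 by age | supports probable bacterial |

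The exact branches are in Figures 2 and 3, which were not available.

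**3. Illustration of size.** Inputs from the document: P(CRP below 20 given bacterial) = 1 − 0.78 = 0.22; P(CRP above the high cutoff given viral) = 1 − 0.85 = 0.15, the limit of the cited specificity. Assumptions, none of them given in the document:

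- 45:14 is the true viral to bacterial ratio.
- A share s of both groups is labelled by CRP alone and the rest are labelled correctly.
- CRP is 0.3 to 0.7 sensitive at each cutoff; a is the value for viral and b for bacterial cases, taken as equal.
- MxA is perfect.

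Formulas:

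- viral labelled viral: 45(1 − s) + 45·s·a; viral labelled bacterial: 45·s·0.15
- bacterial labelled bacterial: 14(1 − s) + 14·s·b; bacterial labelled viral: 14·s·0.22

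Worked case, s = 0.25 and a = b = 0.5: these are 39.375, 1.688, 12.25 and 0.77.

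- Apparent sensitivity = 39.375 / (39.375 + 0.77) = 0.981.
- Apparent specificity = 12.25 / (12.25 + 1.688) = 0.879.
- Mean difference = 500 × (1 − 0.019 − 0.121) = 430 µg/l.

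Power uses Φ(difference / SE − 1.96). Each group's variance is that of the mixture, for example sens·1000² + (1 − sens)·300² + sens(1 − sens)·500² for the labelled-viral group.

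| Share decided by CRP | Apparent sensitivity | Apparent specificity | Difference, µg/l | Power, 42 per group | Power, 135 vs 42 |
|---|---|---|---|---|---|
| 0 | 100% | 100% | 500 | 87% | 99.9% |
| 10% | 99% | 95% | 472-473 | 82% | 99.5% |
| 25% | 98% | 87-89% | 426-433 | 71-72% | 96-97% |
| 50% | 95-96% | 73-78% | 340-370 | 47-56% | 76-85% |

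The loss falls mainly on apparent specificity, because viral cases outnumber bacterial ones and a small fraction of them makes up a large part of the bacterial group.

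**4. Limits of the illustration.** The 45% and 14% are class frequencies under the TREND definition in x-ray-verified CAP, so they may already contain CRP mislabelling. A bacterial case with low CRP also needs a detected virus to be called viral, and some high-CRP viral cases may be classed as mixed; the calculation ignores both. It also assumes that MxA errors are unrelated to CRP errors. The table shows the mechanism and is not an estimate.

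**The case against.** The strongest case against rests on four points.

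- **CRP does not decide most labels by itself.** The four definitive viruses and adenovirus bypass the CRP rule, the viral rule also needs a detected virus, fever must exceed 24 hours, and mixed and undetermined classes exist. This stands, and it confines the point to labels that depended on CRP. The fever condition, however, deals with a CRP that is still rising; it does not remove the overlap of CRP between etiologies.
- **The Introduction and the algorithm do not flatly contradict each other.** The Introduction says not proven, and only for mild or moderate disease; the algorithm uses outer, age-specific cutoffs. The article also concedes that no optimal reference exists and defends a pragmatic choice. This stands: it is a tension. But nowhere does the article discuss what CRP in the reference does to the MxA estimate.
- **The strict algorithm is a safeguard.** Only in part. It is a complementary subanalysis, it ignores adenovirus detections, and the Figure 3 caption still lists CRP among its abbreviations. The text does not settle whether it is free of CRP.
- **Reporting by label route is detail for an analysis plan.** Fair as to the reporting, and such a plan may exist. The reference standard itself, however, is fixed in this article.

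A reader might also infer that the design makes it impossible to show that MxA improves on CRP. The document does not support that reading: no objective or planned analysis compares the two markers, and a substantial class of viral labels does not need CRP below 20.

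**Conclusion.** The point holds for cases whose viral or bacterial label in the main algorithm depended on a CRP cutoff. There, a CRP error is scored against a correct MxA, or the child may leave the comparison.

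A reader might conclude that every disagreement between a correct MxA and a wrong CRP is recorded as an MxA error, or that CRP simply is the reference in the unclear cases. The text does not support either: CRP is one of several inputs, and some of the disagreements may end as undetermined or mixed.

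The size is unknown because the share decided by CRP is not given. Under the assumptions above, a 10% share is minor, a 25% share takes about 11 to 13 points off the apparent specificity of a perfect MxA, and a 50% share about 22 to 27 points. At the expected 135 viral and 42 bacterial cases, power stays at about 96-97% with a 25% share, so the main harm is to the interpretation of accuracy rather than to the test of the mean difference. The direction could differ if MxA and CRP err together, or if the children who drop out are the hard ones. This is a worthwhile and inexpensive improvement, not a flaw that invalidates the study.

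**What to change.** - Derive, for each case, a flag that says whether its class would have been different or undetermined without a CRP cutoff.
- Report the viral versus bacterial MxA results for all cases and separately for cases labelled with and without CRP. Interpret the CRP-labelled stratum as partly agreement with CRP.
- Report how many children with a virus other than RSV, hMPV, influenza, PIV and adenovirus and CRP of 20 or more fall into each class, including undetermined.
- Make the strict-algorithm subanalysis free of CRP, or state that it already is, since the Figure 3 caption lists CRP.

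A pooled estimate corrected for misclassification is not advised. It would need CRP sensitivities and an assumption about the dependence of MxA and CRP given etiology, and the article supplies neither.

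Cost: one derived variable and some analysis wording, with no new data. The bacterial group labelled without CRP will be smaller than the expected 42, so its interval will be wider.

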### Etiology of Childhood Community-Acquired Pneumonia

Defining etiology in childhood CAP is complex [18]. Until recently, our conception of CAP etiology has largely relied on early lung-aspirate studies from the 1970s to 1980s [19]. Vaccination against *Streptococcus pneumoniae* and *Haemophilus influenzae* type B, the 2 major causative agents in childhood CAP, has been introduced in most parts of the world during the last two decades, coinciding with a global decrease in childhood CAP mortality [20]. This has also contributed to a shift in the etiology of CAP [21,22]. Other important factors include a globally improved socioeconomic and nutritional status, a sharp decrease in the incidence of measles, and the emergence of HIV [5]. Recently, new CAP etiology studies, including the large-scale Pneumonia Etiology Research for Child Health (PERCH) study, have been conducted, mostly with a low-income country focus [21-24]. These have pointed toward an underestimation of viral and mixed viral-bacterial etiologies, which is likely explained by the aforementioned shift in etiology but also by the recent advances in viral diagnostics [25]. Moreover, *Bordetella pertussis* and *Bordetella parapertussis*, the causative agents of whooping cough, have been associated with CAP [21,26]. These bacteria are highly contagious and can cause severe disease, particularly in infants [27]. Recent studies have reported an increasing incidence of *B pertussis*, and there have been several deaths in previously healthy infants associated with whooping cough in Sweden over the last 10 years [28,29]. Consequently, there is a need for new updated studies on CAP etiology in various settings.

### A Need for Rapid Microbiological Point-of-Care Tests

Current treatment options with antivirals for respiratory viruses are limited. However, there are several new antivirals that are being developed [30], and furthermore, there is a value in diagnosing viral infections to predict the clinical course and infectivity and to give confidence to withhold the prescription of antibiotics. Real-time PCR is a sensitive molecular-based method that is currently considered gold standard for the detection of respiratory viruses in children with respiratory tract infection [25]. Nevertheless, as PCR usually has to be run in central laboratories and requires complex instrumentation, the turnaround time can be long and the test results are rarely used for decision making regarding treatment at the point of care. There are currently several new antigen-based point-of-care tests for respiratory infections on the market. One is the multianalyte point-of-care antigen detection test system (mariPOC) respi, ArcDia International Oy Ltd, that uses a 2-photon excitation assay technique to detect 10 different respiratory viruses (influenza A/B, respiratory syncytial virus [RSV], adenovirus, bocavirus, coronavirus, human metapneumovirus [hMPV], and parainfluenza virus [PIV] 1-3) [31]. The advantage of the test is that it gives a preliminary result of strongly positive samples already after 20 min and a final result (including negative results) within 2 hours, which potentially allows for immediate treatment considerations. In children, the mariPOC respi’s sensitivity for RSV and influenza virus has been reported to be as high as 90% as compared with PCR, but the sensitivity for less common respiratory viruses, such as hMPV and PIV, and the newly included coronavirus and bocavirus has been insufficiently investigated [32,33].

Recombinase polymerase amplification (RPA) is a nucleic acid amplification technique that does not require thermal cycling. An RPA-based point-of-care test could combine the advantage of high sensitivity with short turnaround time. An RPA-based test using a paper-based vertical flow microarray technique is currently being developed by our partners at the Science for Life Laboratory (SciLifeLab) [34-37]. As the test reaction is carried out at room temperature, it is an interesting method for resource-limited settings where the need for new diagnostic tests is particularly high [38,39].

### Long-Term Complications of Community-Acquired Pneumonia

Studies on the long-term outcomes of radiologically confirmed bacterial CAP have indicated that the disease is associated with later development of asthma and decreased lung function [40,41]. However, most of these studies have followed children who were born more than two decades ago, and the risk might therefore not generalize to a modern setting, given the reported shift in etiology of pediatric CAP [42]. Hence, there is a need for new studies of long-term complications from pediatric CAP, such as the development of asthma and the risk for future respiratory infections.

In summary, there is a need for (1) assessing the diagnostic accuracy of MxA as a biomarker for viral childhood CAP; (2) new studies on clinical CAP etiology in children; (3) evaluating the antigen-based point-of-care test mariPOC; (4) evaluating a novel RPA-based point-of-care test developed at SciLifeLab; and (V) assessing long-term complications from CAP, including the risk of developing asthma and the risk for future respiratory infections.

The overarching aim of the Trial of Respiratory infections in children for ENhanced Diagnostics (TREND) study is to improve the differential diagnosis of bacterial and viral etiologies in children aged below 5 years with clinical CAP. The specific objectives of the study are as follows:

the diagnostic accuracy of MxA for viral CAP in childrenetiology of children with CAPsensitivity and specificity for the mariPOC respi test for the detection of respiratory virusessensitivity and specificity for a novel RPA-based point-of-care test for the detection of respiratory viruseslong-term complications in children with CAP.

